### Outcome predictions

We have created an approach, which is described in Supplementary File  *S3*, to forecast a patient’s future serum creatinine trajectory. *Figure 3* shows the application of the statistical models in predicting future serum creatinine measurements. Predicted pathways (a) and (b) cross the WRF threshold within 12 months, while pathway (c) does not. By forecasting potential creatinine trajectories, we could construct an empirical cumulative distribution for the probability of WRF over time (*Figure 4*). Using the estimated joint model, we will make dynamic predictions for competing secondary outcomes by deriving cumulative event probabilities based on a patient’s observed serum creatinine process, covariate history, and outcome-free survival up to the current time. This will be achieved via Markov chain simulation (Metropolis-Hastings algorithm) and a Monte Carlo process.^34^

**Figure 3 ztag055-F3:**
[figure not shown]
An illustration of serum creatinine pathway prediction using statistical models.

**Figure 4 ztag055-F4:**
[figure not shown]
Probability distribution for WRF within 12 months from the current serum creatinine measurement point.

Secondary outcome risks will be assessed using (i) cause-specific Cox regression models with ridge penalization and (ii) Cox proportional hazard models to subsets of patients who remain in the risk set—i.e. those who have not experienced secondary outcomes or been censored before pre-specified landmark time points.^35^ Additionally, we will explore joint latent class model, where patients are assumed to belong to a single latent class, defining the association between the longitudinal and survival sub models.^36^

### Machine learning modelling

#### Data pre-processing for machine learning

The same longitudinal data from electronic health records that will be used to develop the statistical models will be used to develop the RNN-LSTM model. Although the first stages of data preparation are the same for both modelling strategies, more preprocessing is needed for the ML approach.^37,38^ For neural networks to process data, all variables need to be transformed into a numerical format. Using one-hot encoding, categorical variables like smoking status and gender will be converted to binary indicator variables (0,1) for every category level. We will use log transformations to normalize the distributions of continuous variables, such as serum creatinine, urea, potassium, and sodium, lessen the effect of outliers, and enhance model convergence during training. We will use masking and padding strategies to produce consistent sequence lengths. This will help to solve the problem of inconsistent time series lengths across patient records.^39^ Specifically, short sequences will have zeros padded at specific locations, and the neural network’s masking layer will make sure that these padding values don’t affect the model’s predictions. The details of RNN-LSTM model development are provided in Supplementary File  *S4*.

### Dynamic renal test recommendation system

Dynamic renal test recommendation system module aims to dynamically recommend renal tests based on inputs from the main model. The system proposes time to renal blood test using NICE (National Institute for Health and Care Excellence) guideline as backbone. The proof-of-concept R code is provided in Supplementary File  *S4*. The RNN-LSTM model (Main model) would provide estimations of future serum creatine levels based on historic data of a patient. The NICE guideline offers thresholds and requirement for assessing renal function and identifying WRF. We will adopt the RNN-LSTM prediction model's output to inform the NICE guideline recommendations.

### Explainability

We will use SHAP (SHapley Additive exPlanations) values to apply explainability techniques to address the “black box” nature of deep learning models^40^. To handle sequential data, we will modify the SHAP framework for the time-series LSTM model. This will involve calculating feature importance at each time step and then combining these values to determine both temporal patterns of influence and global feature importance. This approach will quantify how each input variable contributes to predictions across different time points. With this method, the contribution of each input variable to predictions at various time points will be quantified.

### Model assessment

Model assessment refers to the evaluation of predictive accuracy, discrimination, and calibration in a development dataset. On the other hand, validation evaluates the performance of the model in completely invisible (non-local or regionally external) datasets. For each of the three modelling strategies, both assessment and validation steps will be carried out. Detailed mathematical definitions of these metrics are provided in Section 3 of Supplementary File  *S3*. The assessment of these parameters will be as follows:

#### Predictive accuracy

Assessed using the root mean squared prediction error (RMSPE) to quantify the average distance between predicted and observed creatinine levels.

#### Calibration

Evaluating the agreement between predicted probabilities and observed event rates across risk groups.

#### Discrimination

Using the C-statistic to measure the model’s ability to distinguish between patients who will and will not experience WRF.

#### Clinical utility

To assess the practical value of the models, we will perform decision curve analysis. This method calculates the ‘Net Benefit’ of using the model to guide monitoring decisions across a range of threshold probabilities, comparing it against default strategies (e.g. monitoring everyone or no one). We will use methods described in previous research studies to calculate net benefits.^41,42^

### Validation

For validation purposes, we will use a combination of split-sample and internal-external validation approaches.^43^ Internal-external validation will be used to demonstrate external validity.^44^ To prevent data leakage, the entire modelling pipeline including imputation (Random Forest), variable transformation, and feature selection will be performed independently within each training fold before being applied to the validation region. The CPRD Aurum data are drawn from nine geographical regions within England. By region, the data will be split, at the practice level, on a 4:1 ratio for development and external validation purposes. The internal validation will be carried out by considering eight out of nine regions for training and the left-out region will be used for validation. This process will result in nine models that are internally validated. *Figure 5* illustrates one such internal-external validation where region a is left out to cross validate a model developed in the other regions. The final model would be trained on all development data (nine regions) and will be validated against the holdout validation data (20%).

**Figure 5 ztag055-F5:**
[figure not shown]
Proposed regional internal-external cross-validation and subsequent external validation.

The performance measures will be pooled using random effect meta-analyses.^45^ This will also facilitate assessments of between-region variability (heterogeneity) of performance, which will be quantified by the between-region standard deviation of each model performance measure.^46^ Following meta-analysis, the performance measures will be reported as point estimates with 95% confidence and prediction intervals. The confidence intervals will quantify the precision of the average performance of the models across the different geographical regions. The prediction intervals will account for the heterogeneity across regions and will therefore function as an indicator of the expected performance within a specific region and illustrate the various performance measures that will be derived and meta-analysed for the primary outcome.

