**Methods and results:**

This study will use electronic health records from the Clinical Practice Research Datalink (CPRD) database for patients who were diagnosed with HF. We will develop three prediction models—Mixed-effects model, Growth mixture model, and recurrent neural network-long short-term memory model to predict future worsening renal function, including events that lead to hospitalization, and death. Using an internal-external validation approach based on geographic region, we will choose the top-performing model using various metrics to evaluate the predictive performance.

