There are several validated CPMs for the prediction of the onset and progression of chronic kidney disease (CKD) and for stratification of risk in patients with HF. These models focus on outcomes such as risk of admission and readmission, renal complications, and mortality.^3–10^ However, most of these models focus solely on static risk factors and do not directly deal with the dynamic changes in renal function over time. It is worth noting that comparative studies such as Christodoulou *et al*. showed the abilities of machine learning (ML) models and traditional statistical prediction methods in the clinical field.^11^ This study builds on this evidence base by explicitly comparing methods for the personalized monitoring of renal function in HF patients using statistical and ML frameworks.^12–16^

In this study, we provide a detailed scientific protocol for developing, validating, and comparing CPMs. This protocol directly compares three modelling strategies: mixed effects and growth mixture models (representing statistical approaches) and the recurrent neural network-long short-term memory (RNN-LSTM) model (an ML approach), applied to longitudinal electronic health records data from HF patients for the prediction of WRF over a 12-month horizon.

These models will be assessed using various evaluation metrics such as model performance, sustainability, interpretability, parsimony, novelty, implementation, and fairness. These metrics will help to identify the most suitable model to be used in a future clinical trial. This article describes the study protocol in three main stages: the development of WRF predictive models, the validation process of the models, and the selection of the final model for a clinical trial.

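### The article sets out to compare three models directly, but the inference it states describes each model separately and gives no measure of uncertainty for the difference between them

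*Protocol article*

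**What the plan says.** The Introduction states the comparative aim: "This protocol directly compares three modelling strategies". The Abstract (Methods and results) states the decision that follows: "we will choose the top-performing model using various metrics to evaluate the predictive performance".

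The design gives matched performance data. Under Data pre-processing for machine learning, "The same longitudinal data from electronic health records that will be used to develop the statistical models" also feed the RNN-LSTM. Under Model assessment, "For each of the three modelling strategies, both assessment and validation steps will be carried out". Under Validation, "The CPRD Aurum data are drawn from nine geographical regions within England", and each region is left out in turn.

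The inference is set out in the Validation text after Figure 5: "The performance measures will be pooled using random effect meta-analyses". Heterogeneity is summarised by the between-region SD of each measure, and "Following meta-analysis, the performance measures will be reported as point estimates with 95% confidence and prediction intervals". The article also says what the intervals mean: "The confidence intervals will quantify the precision of the average performance of the models across the different geographical regions". The prediction intervals are for expected performance in a particular region.

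Two other sections bear on choosing a model. Clinical utility sets net benefit against monitoring everyone or no one. Model selection measures accuracy by RMSPE and passes the choice to a RAND/UCLA consensus exercise over several criteria.

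**The concern.** The stated outputs answer how well each model does on average and how much that varies by region. The stated question is which model does better, and by how much. That question needs an estimate of the difference, with its own uncertainty.

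The gap matters because the design is paired. A region with an unusual case mix or testing pattern is likely to raise or lower the performance of all three models together. That shared movement widens every model-specific interval, although it says little about which model is better. A within-region difference removes most of it.

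The panel must weigh predictive performance against simplicity, novelty, sustainability and the rest. For that it needs to know whether a lead of, say, 0.01 in the C-statistic is consistent across regions or within noise. Three separate intervals cannot tell it that.

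**Working it through.** **What the text contains.** The sections that could hold a between-model contrast are Model assessment, Clinical utility, Validation and Model selection. None forms a difference between strategies, gives an interval for one, or sets a margin. The article states no figure for a between-model comparison, so there is none to reproduce.

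**Inputs.** From the article: K = 9 regions, three strategies, 95% intervals. Assumed, because the article gives no values: between-region SD of the C-statistic τ = 0.02; within-region SE s = 0.006; between-model correlation of region effects 0.8; between-model correlation of within-region sampling errors 0.8; equal weights; t-based intervals with 8 degrees of freedom (t = 2.306).

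**One model.**
- Variance of a regional estimate: τ² + s² = 0.000400 + 0.000036 = 0.000436.
- SE of the mean over nine regions: √(0.000436/9) = 0.00696.
- Interval width: 2 × 2.306 × 0.00696 = 0.032. With the SD estimated from nine regions, the average width is about 0.031.

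**Paired difference between two models.**
- Variance of a regional difference: 2τ²(1 − 0.8) + 2s²(1 − 0.8) = 0.000160 + 0.0000144 = 0.0001744.
- SE of the mean difference: √(0.0001744/9) = 0.0044.
- Interval width: 2 × 2.306 × 0.0044 = 0.020.

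**Difference built from the two separate SEs, ignoring the pairing.** SE = √2 × 0.00696 = 0.0098, which is 2.24 times the paired SE (1/√(1 − 0.8) = 2.24).

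**Dependence on the correlation of region effects** (other inputs unchanged).

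| Correlation | SE of paired difference | Average 95% interval width |
|---|---|---|
| 0 | 0.0095 | 0.043 |
| 0.5 | 0.0068 | 0.030 |
| 0.8 | 0.0044 | 0.020 |
| 0.95 | 0.0025 | 0.011 |

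At a correlation of 0.5 the difference is estimated about as precisely as a single model's performance. At zero almost nothing is gained over the unpaired SE of 0.0098.

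**Ranking by point estimate, two models.** The better model ranks first with probability Φ(advantage/SE). At an advantage of 0.01 this is Φ(0.01/0.0044) = 98.8%; at 0.02 it exceeds 99.99%. At a correlation of 0.5 the value for 0.02 is 99.8%.

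**Power of the paired interval in the base case** (noncentral t, 8 degrees of freedom). An unadjusted 95% interval excludes zero in about 98% of studies at an advantage of 0.02 and about 52% at 0.01. With Bonferroni over three contrasts (critical value 3.016) this falls to about 90% and 30%.

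**The case against.** Four objections carry weight.

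- **Nothing in the Validation text is wrong as description.** Pooling each measure with confidence and prediction intervals is sound and should stay. This stands. The point is that the article says what these intervals are for, and that purpose is not the comparison it announces.
- **The article is condensed.** Supplementary File S3 holds the metric definitions and S5 the selection criteria, and neither is shown. A contrast could be there, so the statement is limited to the article text.
- **Point estimates already rank the models, usually correctly.** This also stands. A reader might infer that the plan risks choosing the wrong model; the ranking probabilities above do not support that. The loss is in knowing how firm the lead is.
- **Selection is a consensus over several criteria, not a significance test.** True, but accuracy and generalizability are among those criteria, and trading them against others needs the size and certainty of the difference.

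A reader might also infer that models will be judged by whether their intervals overlap, that overlap will count as a tie, and that the choice will then fall to the non-statistical criteria. The article states no such rule, and those criteria apply in any case. A power comparison against interval overlap would therefore test a procedure that the article does not propose.

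**Conclusion.** The point holds in a limited form. The article announces a direct comparison and a choice, its design gives fully paired performance data, and its stated inference stops at separate summaries of each model. The panel would receive a usable ranking but no valid and precise statement of uncertainty about the lead.

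In the base case the paired SE is 0.0044, against 0.0098 when the pairing is ignored. That rests wholly on assumed values for the C-statistic. The gain depends on how strongly regional performance moves together across models: it is larger at 0.95 and nearly vanishes at zero. High correlation is plausible, because the models share patients and regions, but the article does not give it. Even without a gain in precision, an interval for the difference would answer the stated question, and the separate intervals do not.

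The change is worth making because it costs little; it is not a flaw that invalidates the study.

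**What to change.** In the Validation section, add the between-model contrast to the pooled analysis:

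- For each left-out region and each pair of strategies, compute the difference in every measure already planned for worsening renal function (RMSPE, C-statistic, calibration, net benefit) on the same patients.
- Obtain its SE by a paired method, such as a practice-level bootstrap that uses the same resample for all three models.
- Pool the nine differences by random-effects meta-analysis, with 95% confidence intervals from a small-sample, t-based method.
- Give these differences to the consensus panel described under Model selection, and keep the model-specific intervals as descriptions.

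Control over all three contrasts is optional for a consensus decision. If simultaneous intervals are wanted, use Bonferroni, since Holm's step-down procedure does not directly yield intervals, and quote the adjusted power (about 90% at an advantage of 0.02 and 30% at 0.01 in the base case).

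Report any contrast in the 20% hold-out only after selection, so that the hold-out stays untouched for validating the chosen model.

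The cost is a small amount of analysis code and computing. The regional contrasts need no new data and no new model fits, because each strategy is already to be validated in each region.

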### Model selection

The final model selection process will include an assessment of transparency and explainability of the three candidate models. A consensus exercise will be undertaken using the RAND/UCLA appropriateness method.^47^ In addition, our model selection criteria will be accuracy, generalizability, implementability, interpretability, novelty and innovation, simplicity, and sustainability. The model selection criteria are detailed in Supplementary File  *S5*. Accuracy is quantified using RMSPE on both training and independent datasets, while fairness ensures that predictions are equitably accurate across diverse demographic groups. In this study protocol, we will be using the predictive parity (or calibration fairness) framework. Generalizability assesses the model's ability to function far beyond its development context, and implementability assesses how easy it is to integrate into the practice for decision-making. Interpretability refers to the overall clarity of the model for effective correction and bias screening, without focusing on individual case explanations. Novelty and innovation assess the introduction of new techniques or methods, while parsimony favours simpler models with fewer variables to reduce the risk of overfitting. Finally, sustainability ensures that the model can be updated effectively and maintained with minimal expenditure on resources in the event of new data becoming available.

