### Outcomes

The primary endpoint of the study will be worsening of renal function. Early detection or prediction of WRF provides an opportunity for intervention to prevent progression to renal failure and acute kidney injury (AKI) and potentially prevent hospitalization and death. Serum creatinine was selected as the primary biomarker for modelling. While a retrospective glomerular filtration rate (eGFR) recalculation using a single formula (CKD-EPI 2021) was a way of standardizing the historical data, we decided on raw serum creatinine. This approach avoids any bias. The raw serum creatinine allows an ML model to learn the effect of age and gender on renal trajectories directly from raw data rather than being constrained by fixed eGFR coefficients. In addition, a 12-month prediction period has been chosen to align with routine chronic disease monitoring intervals in primary care, thereby bridging the gap between acute injury (AKI) and long-term disease progression. Therefore, WRF is defined by primary care data if any of the following occur within 12 months: (i) 30% increase in serum creatinine or (ii) 26.5 µmol/L increase in serum creatinine.

Secondary outcomes will include hospitalization for AKI, major adverse cardiovascular events (MACE) and all-cause mortality. These outcomes are included specifically to consider competing risks and to recognize that patients with HF may experience cardiovascular events or death before renal monitoring.

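### The accuracy criterion for choosing among the three models is RMSPE on creatinine, training data included, with no WRF measure named; the test recommender is meanwhile tied to the RNN-LSTM

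*Protocol article*

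**What the plan says.** All references are to the protocol article.

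- **Endpoint.** Outcomes: "The primary endpoint of the study will be worsening of renal function". It is met within 12 months by either of two rises: "i) 30% increase in serum creatinine or (ii) 26.5 µmol/L increase in serum creatinine".
- **Planned performance measures.** Model assessment applies to all three strategies: "Model assessment refers to the evaluation of predictive accuracy, discrimination, and calibration in a development dataset", followed by validation in unseen data. Its subsections define RMSPE as a way to "quantify the average distance between predicted and observed creatinine levels", calibration as agreement of predicted probabilities with observed event rates, and discrimination thus: "Using the C-statistic to measure the model’s ability to distinguish between patients who will and will not experience WRF". Clinical utility adds net benefit. Validation pools the performance measures for the primary outcome over regions.
- **Selection.** Model selection lists seven criteria: accuracy, generalizability, implementability, interpretability, novelty and innovation, simplicity, and sustainability. It adds fairness, assessed by predictive parity or calibration across demographic groups. A RAND/UCLA consensus exercise is planned, and Supplementary File S5 gives the details. On the first criterion: "Accuracy is quantified using RMSPE on both training and independent datasets". The abstract says "we will choose the top-performing model using various metrics to evaluate the predictive performance".
- **Recommender.** Dynamic renal test recommendation system: "The RNN-LSTM model (Main model) would provide estimations of future serum creatine levels". The section goes on to say that this model's output will be adopted to inform the guideline recommendations.

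**The concern.** Three things do not fit together.

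1. The one predictive measure that the selection text names concerns the level of creatinine. The endpoint is whether a patient crosses a rise threshold within 12 months. The measures that address that question are planned but are not tied to any selection criterion.
2. Error on the data used to fit a model is apparent performance. It tends to fall as a model becomes more flexible, whether or not prediction in new patients improves. The article lists it beside independent error under accuracy, with no statement of its role.
3. The recommender section already names one of the three candidates as its engine, while the abstract, Introduction and Model selection leave the choice open.

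The Introduction says the metrics will help to identify the model for a future clinical trial. At stake is whether that trial carries the model that predicts WRF best, and whether the recommender runs on the model that was chosen.

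**Working it through.** The article gives no figure on this point to reproduce. The check compares its sections and then asks, with assumed inputs, whether the mismatch could matter.

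**Step 1: sections side by side.**

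| Measure | Planned for the models | Named as a selection criterion |
|---|---|---|
| RMSPE on creatinine | Yes (Predictive accuracy) | Yes, as accuracy |
| C-statistic for WRF | Yes (Discrimination) | No |
| Calibration of predicted probabilities | Yes (Calibration) | Only as fairness across demographic groups |
| Net benefit | Yes (Clinical utility) | No |

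**Step 2: can RMSPE and WRF performance disagree?** Assumed inputs, none from the article: 200,000 simulated patients; baseline creatinine log-normal around 100 µmol/L with log-scale SD 0.35; 12-month log change = 0.03 + 0.10 × predictor + residual, with a standard normal predictor and residual SD 0.20. WRF is as the article defines it: follow-up at least 1.3 × baseline, or at least 26.5 µmol/L above it. The WRF rate is 19.9%.

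- Model A ignores the predictor. Its SD of log change is √(0.10² + 0.20²) = √0.05.
- Model B uses the predictor but predicts creatinine 14% too high.

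RMSPE = √mean[(observed − predicted)²]; O/E = observed WRF rate ÷ mean predicted risk.

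| | RMSPE (µmol/L) | C-statistic | O/E |
|---|---|---|---|
| A | 26.9 | 0.60 | 0.1991/0.1993 = 1.00 |
| B | 29.4 | 0.74 | 0.1991/0.3933 = 0.51 |

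RMSPE and calibration prefer A; discrimination prefers B. B's fault is a constant factor that recalibration could remove, while A lacks the information that separates patients. RMSPE alone does not reveal this.

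**Step 3: what does training RMSPE reward?** Assumed: ordinary least squares without regularisation, n = 500, residual SD 25, five real predictors, one simulated data set per row. As a check, expected training RMSPE is about 25√(1 − k/n) and expected independent RMSPE about 25√(1 + k/(n − k − 1)), for k parameters.

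| k | Training, simulated | Training, formula | Independent, simulated | Independent, formula |
|---|---|---|---|---|
| 5 | 25.9 | 25√0.990 = 24.9 | 24.9 | 25√(1 + 5/494) = 25.1 |
| 50 | 24.5 | 25√0.900 = 23.7 | 27.3 | 25√(1 + 50/449) = 26.4 |
| 200 | 18.4 | 25√0.600 = 19.4 | 31.6 | 25√(1 + 200/299) = 32.3 |

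Training error improves while independent error worsens. This shows direction only; it is not a model of the planned design.

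**Step 4: recommender.** The recommender section names the RNN-LSTM both as main model and as the source of the adopted output. Model selection refers to three candidates still to be judged. The two statements cannot both stand as written.

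**The case against.** The strongest reply is that accuracy is one of several criteria in a consensus exercise, that S5 (not shown) details them, and that the abstract and Introduction speak of various metrics and model performance. Nothing says the panel will be denied the WRF results. This stands, so a reader who infers that RMSPE alone decides, or that WRF performance is never assessed, goes beyond the text. It does not remove the point: the article itself defines accuracy, and that definition omits the endpoint.

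RMSPE is also a legitimate measure. The study models the creatinine trajectory on purpose and derives WRF risk from it, and the article uses the term predictive accuracy for RMSPE throughout. That supports keeping it, not letting it stand alone.

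Reporting training beside independent error is a normal way to show optimism, and the article never says that training RMSPE ranks the models. The inference that selection will reward overfitting is therefore not established. Counting network weights does not establish it either: dropout, early stopping, region-out validation with the pipeline refitted in each fold, and at least 36,000 patients all bear on overfitting, and a raw count reflects none of them.

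A reader might also infer that RMSPE ranks models mainly on patients with high creatinine. That would need an assumed spread of creatinine and error proportional to level. The scale of RMSPE is not visible (its definition is in Supplementary File S3), and on a log scale the effect would vanish under the same assumption.

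The rank reversal in Step 2 depends on a bias given to model B, which a calibration criterion would also penalise. It shows possibility only.

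Finally, the recommender comes with proof-of-concept code and commits no trial to the RNN-LSTM. That softens the conflict of wording but does not resolve it.

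**Conclusion.** The point holds as a should-fix. As written, the accuracy criterion rests only on creatinine RMSPE, with the role of training error left open, and no selection criterion names discrimination, overall calibration or net benefit for WRF. The recommender text contradicts the open three-way choice.

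The size of the consequence cannot be taken from the article. The illustrations rest wholly on assumed inputs; they show that RMSPE and WRF discrimination can order two models differently and that training error can mislead, not that either will happen here. If S5 already brings WRF measures into accuracy, what remains is to reconcile the article with it.

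**What to change.** 1. **Model selection** (and S5, if it does not already say so): make calibration, C-statistic and net benefit for 12-month WRF, out of sample and pooled over the nine left-out regions, part of the accuracy criterion. Keep out-of-sample RMSPE as a supporting measure. State that training RMSPE is reported only to describe optimism.
2. **Timing:** say that selection uses the internal-external results. The term independent datasets could otherwise be read to include the 20% hold-out, which the Validation section reserves for the final model.
3. **Recommender section:** replace both references to the RNN-LSTM as the source of predictions with the selected final model.

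The cost is wording in two sections and possibly S5. Every measure is already planned, and pooling over regions is already described, so no new analysis is needed.
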